## Background

Hip fractures constitute an economic burden on healthcare resources that will continue to rise. Approximately 17,000 older persons sustain a hip fracture in the Netherlands every year [1]. Costs of treatment, rehabilitation and home care are considerable (nearly EUR 400 million per year). Regardless of the costs, hip fractures have a negative effect on activities of daily living and quality of life. One year after the fracture, less than 50% of patients have fully recovered [2]. Most persons with a fracture undergo surgery. However, perioperative care in hip fracture patients leaves much room for improvement, as convalescence after surgery is often hindered by complications. As a consequence, hip fracture is associated with high mortality and considerable loss of function [3]. Complications may occur in many organ systems and require the involvement of various medical specialties. In theory, the involvement of many specialties should guarantee the best possible treatment, yet in practice the care tends to be rather fragmented. Therefore, it is generally felt that perioperative care can be improved if care is organized in comprehensive care pathways. Aim of care pathways is to optimize care during the entire process of surgery and rehabilitation. The effectiveness of care pathways for persons with a hip fracture was investigated in studies that show a tendency for the pathways being more effective than usual care [4-6]. However, the extensiveness of these care pathways differs and most care pathways deal with only one or a few aspects of the care (e.g. the postoperative rehabilitation in hospital care).

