### Measurements

Measurements will be taken preoperatively, perioperatively, and at 6 weeks and 3 and 6 months after surgery. Preoperative demographic data, preoperative diagnosis, height, weight, Body Mass Index and ASA classification will be recorded. Hip fractures will be classified as femoral neck fractures and pertrochanteric or intertrochanteric fractures. Average surgical time, intraoperative blood loss, in-hospital transfusion rate and complications will be recorded perioperatively. Mortality will also be recorded.

Self-reported limitations in ADL will be measured with the Katz index and Lawton Instrumental Activities of Daily Living (IADL) scoring list [8,9]. The Katz index is based on an evaluation of the functional dependence or independence of patients in bathing, dressing, going to the toilet, transferring, continence and feeding. ADL index A indicates independence in all six functions, index B independence in all but one of the six functions. Indexes C–G indicate dependence in bathing and at least one additional function. The IADL scoring list is an evaluation of the abilities of patients in eight activities: using the telephone and transportation, shopping, preparing food, housekeeping and laundry, responsibility for their own medications and handling finances. On the basis of the score patients are divided into different categories that state something about their degree of independence.

Health-related quality of life will be measured using the EQ-5D (EQ-5D™ Dutch© 1987 Euroquol Group). The EQ-5D has five dimensions: mobility, self-care, usual activities, pain/discomfort, and anxiety/depression. Each dimension is divided into three degrees of severity: no problem, some problems, and major problems. Actual quality of life must also be signed on the EQ VAS scale. The Katz index and IADL scoring list are measured at the hospital (to determine the situation before the fracture) and at 6 weeks and 6 months after the operation. The EQ-5D will be assessed on the same occasions and at 3 months after the operation.

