### Sample size

The power calculation is based on the hypothesis that 15% more patients treated with the new comprehensive care pathway compared with patients in the care-as-usual condition will have recovered at least as well at 6 months follow-up to pre-fracture levels in terms of ADL as measured with the Katz index. In order to detect this 15% difference with 80% power at a significance level of 0.05 (one-sided), 130 patients are needed in the new comprehensive care pathway condition and 130 in the usual care condition. Since a comparison will be made between UMCG and MHG as well as between UMCG and OHW, 130 patients will be included in MHG and 130 in OHW. Taking into account an expected drop out-rate of 15% a total of 450 patients have to be included.

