### Statistical analyses

Statistical analysis will be performed with IBM SPSS Statistics 19.0 (IBM, Amonk, NY). As conventional randomization is not feasible in this patient group, propensity score adjustment will be applied. Propensity scores, or the likelihood to be in the treatment condition or control condition, will be estimated with the following (pre-fracture) variables: age, gender, marital status, living situation, functional status, co morbidity, cognitive function, number of medications, need for home care, need for day care. Propensity scores will be used as an independent variable in the multivariate analysis.

Descriptive statistics will be used to describe the main characteristics of the population. For comparison between UMCG and MHG and OHW a multivariate analysis of variance (MANOVA) will be applied. The Katz index, Lawton Instrumental Activities of Daily Living (IADL) scoring list, the EQ-5D and HHS will be included as dependent variables and hospital and the propensity score as independent variables. A p-value lower than 0.05 will be considered as statistically significant.

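### The hypothesis counts all treated patients, but patients who die before 6 months have no place in the named analysis, so as written the 6-month comparison covers survivors only

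*Protocol article*

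**What the plan says.** The Sample size section of the protocol article puts the hypothesis as a count of patients: "15% more patients treated with the new comprehensive care pathway compared with patients in the care-as-usual condition will have recovered at least as well", judged by the Katz index at 6 months against the pre-fracture level. From this it derives that "130 patients are needed in the new comprehensive care pathway condition and 130 in the usual care condition", with one group per hospital, and then: "Taking into account an expected drop out-rate of 15% a total of 450 patients have to be included". It does not define drop-out.

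The Statistical analyses section names one between-hospital comparison: "For comparison between UMCG and MHG and OHW a multivariate analysis of variance (MANOVA) will be applied". The dependent variables are the Katz index, the Lawton IADL list, the EQ-5D and the Harris Hip Score. The independent variables are hospital and a propensity score estimated from pre-fracture characteristics.

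The Background states that "hip fracture is associated with high mortality and considerable loss of function", and the Measurements section adds "Mortality will also be recorded". Mortality has no role in the analysis section, and no value or category is given to a patient who dies.

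**The concern.** The hypothesis and the analysis do not cover the same patients. The hypothesis takes treated patients as its denominator, and a treated patient who dies has not regained pre-fracture ADL. The MANOVA needs a value on every dependent variable, and a patient who dies before 6 months has none at 6 months. Unless a value is assigned, that patient leaves the 6-month comparison.

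Restricting to survivors conditions on something that happens after treatment and that the pathway may itself affect: the Background motivates better perioperative care by complications and the mortality and loss of function that follow. If survival differs between hospitals, the survivors at each hospital are differently selected groups. The propensity score balances the hospitals at admission only, so it does not restore comparability among those alive at 6 months. At stake are the size of the main result, its power and, under narrower conditions, its sign.

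**Working it through.** **1. The plan's own figure.** Inputs from Sample size: 15-point difference (reading the 15% as percentage points), one-sided 0.05, 80% power. No control rate is stated, so one is assumed.

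n = [1.645·√(2p̄(1−p̄)) + 0.842·√(p₁(1−p₁) + p₂(1−p₂))]² / 0.15²

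- 30% v 45%: [1.645·√0.46875 + 0.842·√0.4575]² / 0.0225 ≈ 128 per group. 55% v 70% gives the same.
- 40% v 55%: 136 per group.
- Total: 3 × 130 = 390; 390/0.85 = 459 and 390 × 1.15 = 449, against 450 stated.

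The 130 and the 450 are reproduced closely enough and are not in dispute. The calculation is for a difference between two proportions of patients.

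**2. Who has a 6-month score.** By the Measurements section, Katz and IADL are taken in hospital (for pre-fracture status), at 6 weeks and at 6 months; the EQ-5D also at 3 months; the Harris Hip Score at the 6-week and 6-month outpatient visits. A patient who dies after 6 weeks can have earlier scores but no 6-month ones.

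**3. Size of the distortion.** The documents give neither 6-month mortality nor 6-month recovery, so all rates here are assumed. The nearest stated figure is that fewer than half have fully recovered at one year (Background). Let the all-patient recovery be c = 0.40 under usual care and t = 0.55 under the pathway, with death counted as not recovered. With death rates d_C and d_T, survivors-only recovery is c/(1−d_C) and t/(1−d_T). Enrolment is 450/3 = 150 per hospital, with no other losses.

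| Deaths, usual care v pathway | Survivors only | Difference | One-sided power |
|---|---|---|---|
| All patients, death = not recovered | 40.0% v 55.0% | 15.0 | 83% |
| 20% v 10% | 0.40/0.80 = 50.0% v 0.55/0.90 = 61.1% | 11.1 | 56% |
| 15% v 10% | 0.40/0.85 = 47.1% v 61.1% | 14.1 | 74% |
| 20% v 20% | 50.0% v 0.55/0.80 = 68.8% | 18.8 | 91% |
| 10% v 20% | 0.40/0.90 = 44.4% v 68.8% | 24.3 | 99% |

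Power for the 20% v 10% row: 150 × 0.80 = 120 and 150 × 0.90 = 135 survivors; pooled proportion (60 + 82.5)/255 = 0.559; SE₀ = √(0.559 × 0.441 × (1/120 + 1/135)) = 0.0623; SE₁ = √(0.25/120 + 0.611 × 0.389/135) = 0.0620; (0.111 − 1.645 × 0.0623)/0.0620 = 0.14, so power is Φ(0.14) ≈ 56%.

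With equal mortality the difference is only rescaled (15/0.80 = 18.75): the question changes, but the sign cannot. With unequal mortality, fewer pathway deaths shrink the apparent gain relative to that, and more pathway deaths enlarge it.

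**4. When the sign reverses.** It reverses when t/(1−d_T) < c/(1−d_C) although t > c. With c = 0.40 and deaths of 20% v 10%, this needs t < 0.50 × 0.90 = 0.45, so an all-patient gain below 5 points. With 20% v 15% it needs t < 0.50 × 0.85 = 0.425, a gain below 2.5 points. Example: deaths 20% v 10%, 50% recovery in patients who survive under either care, 10% in those the pathway saves. Pathway survivors: (0.80 × 0.50 + 0.10 × 0.10)/0.90 = 45.6% v 50.0% (−4.4 points). All patients: 41.0% v 40.0% (+1.0).

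**The case against.** The strongest objection is that nowhere does the article say that deaths are excluded. The exclusion is inferred from the method and its variables. A journal article often leaves missing outcomes and analysis sets to a fuller plan, which is not shown here and may settle the matter. The hypothesis, read plainly, already keeps a deceased patient in the denominator as not recovered. That is fair, and it is why the point is put as a consequence of following the text as written. It does not remove the point: the article itself fixes the hypothesis, the method, the dependent variables and the covariates, and these do not fit together for patients who die.

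Second, the figures above are recovery proportions, whereas the MANOVA compares scores. This also stands. The documents give no means or standard deviations from which to express the effect in score units. The restriction to survivors applies to both, but the size for the MANOVA itself cannot be computed.

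A reader might go further and infer that a life-saving pathway would look harmful. The documents do not support that as the expected result. It takes lower pathway mortality, poor recovery in the patients saved and little gain in everyone else. With the planned 15-point gain and 20% v 10% deaths, the survivors-only difference is still +11.1. Nor do the documents support reading the 15% drop-out as containing the deaths; the text leaves this open.

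**Conclusion.** The point holds in conditional form. The stated hypothesis concerns all treated patients; the only named comparison, applied at 6 months as written, can use only survivors with scores. If mortality differs between hospitals, the comparison is distorted, in a direction that cannot be known beforehand. Under the assumed 40% v 55%, a 15-point gain appears as anything from 11.1 to 24.3 points over the death rates tried. The largest figure arises when the pathway has twice the deaths of usual care. Where the pathway halves deaths from 20% to 10%, power falls from 83% to 56%.

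These sizes rest on assumed mortality and recovery rates, on proportions in place of scores, and on no losses other than death. That deaths drop out is an inference from the method, though a firm one unless a value is assigned to them elsewhere. The pre-fracture propensity score is no remedy under any of these assumptions.

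**What to change.** - Define the primary outcome as binary in all included patients: recovered means alive at 6 months with a Katz index at least at the pre-fracture level; death before 6 months counts as not recovered.
- Compare hospitals on it with a propensity-adjusted binary model, such as logistic regression with hospital and the propensity score as independent variables. The MANOVA cannot serve for this outcome, so changing the endpoint wording alone is not enough.
- State that the 15% drop-out covers living patients without a 6-month Katz.
- Report mortality by hospital beside the primary result.
- Keep the MANOVA on survivors' scores as a secondary analysis, labelled as such.

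The cost is small. Mortality and Katz are already recorded, so no new data are needed, and the sample size was already calculated for a difference in proportions. One more model has to be specified. The outcome combines death with loss of ADL, which is why mortality must be shown separately. If a fuller plan already counts deaths this way, aligning the published text with it is enough.

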### Intervention

In the new comprehensive care pathway of UMCG the treatment and the role of every participant is described from arrival at the emergency room until discharge from the nursing home. This new treatment protocol comprises multidisciplinary cooperation between trauma surgeon, orthopedic surgeon, anesthesiologist and geriatrician, a preoperative workup protocol, a fixed moment of surgery and a postoperative protocol in close collaboration with the physical therapist and nursing home physician. The comprehensive care pathway does not end with discharge from the hospital. The core elements of the pathway are:

– A shared preoperative planning protocol for both the departments of orthopedics and traumatology.

– A perioperative anesthesiological risk assessment in the emergency room already, instead of later on the ward.

– Enrolment of the patients for surgery at a fixed time in the emergency operating rooms (OR). Each morning at 8:00 AM an emergency room with plenum is available for such a patient if necessary. An experienced surgeon and OR team are also available.

– Because of the fixed time of surgery, 8:00 AM on the day after admission, there is allowance for patients to eat until midnight — eight hours before surgery — causing minimal discomfort.

– A uniform treatment protocol for both surgery teams of the departments of orthopedics and traumatology.

– Clustering of all hip fracture patients on one nursing ward in order to use the experience and knowledge of the nursing staff and consequently improve the quality of care for the patient, with extra attention for care of elderly patients (early start of rehabilitation, adequate nutrition, prevention of pressure ulcers and delirium).

– Daily visits by the geriatric team during the stay at the nursing ward.

– Early initiation of standard discharge procedures. Upon arrival at the hospital the patient is already registered for transfer to a nursing home.

– Planned capacity at the nursing homes for an efficient transfer of patients. In addition, the nursing home physician is able to view the data of patients with hip fracture in the data management systems of UMCG. Since this doctor handles the admissions, he/she can view the progress of the patients and anticipate their arrival.

– Patients are seen at a special outpatient clinic for hip fracture patients. The last visit is planned 6 months after the operation. Special attention is paid to functioning in daily living activities.

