At the outpatient clinic, at 6 weeks and 6 months after the operation, fracture consolidation, complications and Harris Hip Score will be assessed [10]. The Harris Hip Score (HHS) is a validated functional hip score that measures four items: pain, function, range of motion and deformity, in that order of importance. A score between 90 and 100 points means an excellent outcome, a score lower than 70 means a poor outcome. Six months after the operation the living and independence situation (percentage of people living in their own home again) of the patient is evaluated.

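### The trial is sized on the proportion regaining their pre-fracture Katz level, but the only hospital comparison named is a MANOVA of four scales that does not test that proportion

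*Protocol article*

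**What the plan says.** The Abstract, the Background and the Sample size section all state one hypothesis. The Sample size section ties it to an instrument: 15% more pathway patients "will have recovered at least as well at 6 months follow-up to pre-fracture levels in terms of ADL as measured with the Katz index". The sizing assumes 80% power at a one-sided 0.05 level and concludes that "130 patients are needed in the new comprehensive care pathway condition and 130 in the usual care condition". It then applies this to two pairwise comparisons: "Since a comparison will be made between UMCG and MHG as well as between UMCG and OHW, 130 patients will be included in MHG", with the same number in OHW.

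The Statistical analyses section names one inferential procedure for comparing the hospitals, a MANOVA. In it, "The Katz index, Lawton Instrumental Activities of Daily Living (IADL) scoring list, the EQ-5D and HHS will be included as dependent variables"; hospital and the propensity score are the independent variables, and p below 0.05 counts as significant. The section mentions no recovered/not recovered variable, no comparison of the 6-month Katz level with the pre-fracture level, no time point and no test of proportions. Pre-fracture functional status appears only as an input to the propensity score.

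**The concern.** The two sections describe different questions. The sizing asks whether a larger share of UMCG patients regain their own earlier Katz level. The MANOVA asks whether the mean vectors of four scales differ between hospitals in any way. Someone who follows the article as written obtains neither an estimate nor a p-value for the stated hypothesis.

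Three consequences follow. A significant result need not involve ADL at all. The test has no direction, although the sizing is one-sided. The 80% power statement does not describe the test to be run. The Katz index, described under Measurements as ordered categories A to G, is also a poor fit to a method built for multivariate normal outcomes, although the article does not say how it would be coded.

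**Working it through.** **Step 1: reproduce the plan's figure.** Inputs from the Sample size section: difference 0.15, one-sided 0.05 (z = 1.645), 80% power (z = 0.842), 1:1. The control recovery rate p1 is not given. I assume 0.30 to 0.55; the only related figure, in the Background, is that under 50% have fully recovered at one year. With p2 = p1 + 0.15 and p̄ their mean:

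n = {[1.645·√(2p̄(1−p̄)) + 0.842·√(p1(1−p1) + p2(1−p2))] / 0.15}²

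- p1 = 0.30: [(1.645×0.6847 + 0.842×0.6764)/0.15]² = 127.8, so 128 per arm
- p1 = 0.425: [(1.645×0.7071 + 0.842×0.6991)/0.15]² = 136.3, so 137 per arm (the maximum)
- p1 = 0.55: 128 per arm, by symmetry with 0.30

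The range of 128 to 137 brackets the stated 130. Reading 15% as a relative increase gives 208 to 1,334 per arm (control rates 0.70 down to 0.30) and does not fit. The trial is therefore sized as a one-sided comparison of two proportions, 15 percentage points apart.

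**Step 2: power of that comparison at 130 per arm.** Power = Φ{[0.15√130 − z·√(2p̄(1−p̄))] / √(p1(1−p1) + p2(1−p2))}, where 0.15√130 = 1.710.

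| p1 | one-sided (z = 1.645) | two-sided (z = 1.960) |
|---|---|---|
| 0.30 | 80.6% | 70.7% |
| 0.425 | 78.3% | 67.9% |
| 0.50 | 79.1% | 68.9% |
| 0.55 | 80.6% | 70.7% |

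**Step 3: can the MANOVA be significant without a Katz effect?** For 130 v 130 and four scales the noncentrality is λ = (130×130/260)·δ′R⁻¹δ = 65·δ′R⁻¹δ, where δ holds the standardised shifts and R the correlations. Assume 0.4 SD on HHS only and uncorrelated scales: λ = 65×0.16 = 10.4. The 4-df chi-square test at 0.05 then has power of about 74% (about 73% with the F distribution). A positive result with no ADL difference is thus entirely possible.

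**Step 4: the MANOVA's power for a Katz-only effect.** Assume a latent-normal Katz shift that matches 42.5% v 57.5%, that is d = 0.378, and equal correlations r. Then λ = 65×0.378²×(R⁻¹)₁₁ = 9.30×(R⁻¹)₁₁.

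| r | (R⁻¹)₁₁ | λ | power (4 df) |
|---|---|---|---|
| 0 | 1.000 | 9.30 | 68% |
| 0.3 | 1.203 | 11.19 | 77% |
| 0.5 | 1.600 | 14.88 | 89% |
| 0.7 | 2.581 | 24.00 | 99% |

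If all four scales shift by d, power runs from above 99% (r = 0) down to about 80% (r = 0.7). The article gives neither the correlations nor the effects on the other scales, so 130 per arm is not a power calculation for this test.

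**The case against.** A condensed article may leave detail to a fuller protocol or SAP that is not shown. That is a fair limit: the point can only be that the analysis described here does not test the hypothesis, not that it will never be tested. But the article does not leave the test open. It names one, and that test does not address its own hypothesis.

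The Abstract's objective is self-reported ADL limitation, which Measurements assesses with both Katz and IADL. Analysing several scales fits that objective, so the MANOVA need not disappear; it cannot be the decision test for the 15% hypothesis. Pre-fracture function is not ignored either, since it enters the propensity score, but that does not create a recovery outcome. Reading the dependent variables as raw scores is the natural reading, although the article does not state their form.

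Two stronger readings are tempting, and the documents do not support them.

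- A reader might infer that the MANOVA dilutes a real Katz effect and that its power falls to about 47%. That figure arises only by putting the binary outcome's noncentrality (0.15²/(2×0.244375/130) = 5.98) into a 4-df test of uncorrelated scales. The MANOVA uses scale scores, and on the matching latent shift its power is 68% or more, and above 80% at the higher correlations.
- A reader might infer that missing HHS values would remove Katz answers unequally between arms, because the pathway includes its own clinic ("Patients are seen at a special outpatient clinic for hip fracture patients"). But Measurements says "At the outpatient clinic, at 6 weeks and 6 months after the operation, fracture consolidation, complications and Harris Hip Score will be assessed" without restricting this to UMCG. The article gives no attendance figures and no missing-data rule, and such a rule is commonly left to the fuller document.

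**Conclusion.** The mismatch stands and should be corrected before analysis. It is a contradiction between two sections of the same article, and nothing elsewhere in it reconciles them. Followed as written, the analysis yields no estimate or p-value for the hypothesis on which the trial was sized, and the 80% power belongs to a different test.

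This core conclusion needs no numerical assumption. The figures do. The power for proportions rests on assumed control rates of 0.30 to 0.55 and ignores the propensity adjustment. The 74% rests on an assumed 0.4 SD shift on HHS alone with uncorrelated scales. The range of about 68% to 99% rests on a Katz-only latent shift of 0.38 SD and equal correlations of 0 to 0.7. That range shows that the MANOVA's power is undetermined, not that it is low. Neither a general loss of power nor selection that differs between arms is established.

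**What to change.** - Define the primary outcome explicitly: Katz level at 6 months at least as good as the pre-fracture level, yes or no.
- Make the primary analysis a propensity-adjusted binary model (logistic or risk-difference) with the contrasts UMCG v MHG and UMCG v OHW. Report the adjusted difference in proportions with a confidence interval, and include every patient with a Katz outcome, whether or not the other scales are available.
- Analyse IADL, EQ-5D and HHS as secondary outcomes. The MANOVA may stay, at most as a secondary analysis.
- State the sidedness of the primary test. If it is one-sided, the existing sizing roughly serves it. If it is two-sided at 0.05, restate the power at 130 per arm as in Step 2; 80% would need about 163 to 174 per arm over the same control rates.

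Keeping the one-sided sizing, or restating the power at 130 per arm, costs only a rewritten analysis section. The Katz index is already planned before the fracture and at 6 months, so no new data or patients are needed. Restoring 80% power for a two-sided test would need more patients.

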## Abstract

**Background:**

Hip fractures constitute an economic burden on healthcare resources. Most persons with a hip fracture undergo surgery. As morbidity and mortality rates are high, perioperative care leaves room for improvement. Improvement can be achieved if it is organized in comprehensive care pathways, but the effectiveness of these pathways is not yet clear. Hence the objective of this study is to compare the clinical effectiveness of a comprehensive care pathway with care as usual on self-reported limitations in Activities of Daily Living.

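### The trial is sized on a one-sided comparison of 6-month Katz recovery, but the only test named is a non-directional MANOVA on four outcomes, which cannot show an ADL difference or its direction

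*Protocol article*

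**What the plan says.** The objective in the Abstract is to "compare the clinical effectiveness of a comprehensive care pathway with care as usual on self-reported limitations in Activities of Daily Living". The Sample size section makes this specific. The hypothesis is a gain of 15% under the pathway in the share of patients who "will have recovered at least as well at 6 months follow-up to pre-fracture levels in terms of ADL as measured with the Katz index". The calculation uses 80% power and a one-sided level of 0.05, and concludes that "130 patients are needed in the new comprehensive care pathway condition and 130 in the usual care condition".

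The Statistical analyses section then describes a MANOVA. "The Katz index, Lawton Instrumental Activities of Daily Living (IADL) scoring list, the EQ-5D and HHS will be included as dependent variables", with hospital and the propensity score as the independent variables. The section ends: "A p-value lower than 0.05 will be considered as statistically significant". It names no separate test of Katz recovery, no direction and no leading outcome. Katz enters as an index, not as the recovered share that the Sample size section uses.

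According to the Measurements section, the HHS "measures four items: pain, function, range of motion and deformity", so it covers more than ADL.

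**The concern.** The hypothesis is about one outcome and one direction. The null hypothesis of the MANOVA is that the hospitals do not differ on any of the four instruments, and the alternative is any difference, in any direction. The test keeps its 5% level only when all four differences are zero. If the pathway, or anything else that differs between the hospitals, affects the HHS alone, the joint test will tend to reject although ADL is unchanged. Effects in opposite directions do not cancel either; with positively correlated outcomes they raise the statistic.

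A reader who sees a significant p-value from the one planned test could therefore take it as support for the ADL hypothesis when it is not. If separate tests on each outcome are read at 0.05 instead, nothing in the article limits the chance of a false positive over the four.

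**Working it through.** **1. The plan's own figure.** Inputs from the Sample size section: difference 15% (read as 15 percentage points), power 80%, one-sided 0.05, 130 per condition. The recovery rate under usual care is not stated, so I ranged it from 0.30 to 0.55.

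n per group = [1.645·√(2p̄(1−p̄)) + 0.842·√(p₁(1−p₁) + p₂(1−p₂))]² / 0.15², where p̄ is the mean of p₁ and p₂.

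- 0.30 vs 0.45: 128. 0.425 vs 0.575: 137 (the maximum). 0.50 vs 0.65: 134. 0.55 vs 0.70: 128.
- Power at 130 per group: 78.3% to 80.6% over the range.
- A two-sided 0.05 test would need 163 to 174.

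So 130 per condition fits a one-sided test of the Katz recovery share, and that is the test the trial is sized for.

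**2. What the joint test detects.** For two hospitals with 130 patients each, the MANOVA is Hotelling's T². With standardised differences d and correlation matrix R, the noncentrality is

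λ = (130·130/260)·d′R⁻¹d = 65·d′R⁻¹d,

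referred to F with 4 and 255 degrees of freedom (254 with the propensity score as covariate; the results are the same to three decimals). I assumed normal outcomes and a common correlation ρ. For these patterns:

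- HHS alone differs by d: d′R⁻¹d = d²(1+2ρ)/[(1−ρ)(1+3ρ)]. For d = 0.4 and ρ = 0.5: 0.16 × 2/(0.5 × 2.5) = 0.256, so λ = 65 × 0.256 = 16.6.
- Katz −0.2 SD and HHS +0.2 SD: d′R⁻¹d = 0.08/(1−ρ). At ρ = 0.5 this is 0.16, so λ = 10.4.

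Probability of p < 0.05:

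| True differences | ρ = 0 | 0.3 | 0.5 | 0.7 |
|---|---|---|---|---|
| HHS +0.3 SD, other three zero | 45% | 53% | 67% | 89% |
| HHS +0.4 SD, other three zero | 73% | 81% | 92% | 99% |
| Katz −0.2 SD, HHS +0.2 SD | 40% | 56% | 73% | 93% |
| All four +0.3 SD | 98% | 81% | 67% | 57% |
| All four −0.3 SD | 98% | 81% | 67% | 57% |

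The last two rows are identical: the test cannot tell benefit from harm.

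**3. Hospital as a three-level factor.** A simulation with 130 patients in each of three hospitals, Wilks' lambda and a covariate gave 85%, 95% and nearly 100% (ρ = 0.3, 0.5, 0.7) for an HHS-only difference of 0.4 SD at the pathway hospital. Under no difference at all the rate was 4.7% to 5.4%, so the test is valid for its own null. That null is not the trial's hypothesis.

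**4. Separate tests at 0.05.** With four independent outcomes, the chance of at least one false positive is 1 − 0.95⁴ = 18.5%. By simulation it is 17.4% at ρ = 0.3 and 15.5% at ρ = 0.5.

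**5. Does the joint test lose power for ADL?** The effect that a single one-sided test detects with 80% power at 130 per group is (1.645 + 0.842)·√(2/130) = 0.308 SD. For that effect a two-sided test of Katz has about 70% power.

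| True differences | ρ = 0 | 0.3 | 0.5 | 0.7 |
|---|---|---|---|---|
| Katz alone +0.308 SD | 47% | 56% | 70% | 90% |
| Katz and IADL both +0.308 SD | 81% | 80% | 88% | 98% |

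Against the two-sided Katz test, the joint test loses power only when Katz alone shifts and the correlation is low.

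**The case against.** The strongest reply is that the article never calls the joint p-value its criterion for success. The 0.05 sentence is a general convention, the ADL target is stated several times elsewhere, and the handling of follow-up tests and multiplicity is commonly left to a full protocol or analysis plan, which is not shown. The first part stands: a reader might infer a declared success rule based on the MANOVA, and the text does not contain one. But the article does not leave the analysis open. It names the test, its dependent and independent variables and the threshold, and that test does not address the hypothesis in the Sample size section. This is a stated analysis that does not fit, not a missing detail.

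Three further readings are tempting and are not supported.

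- A reader might infer that an ADL effect is generally diluted in the four-outcome test. Step 5 shows otherwise. The Measurements section counts both Katz and IADL as ADL measures, and when both shift the joint test has 80% or more.
- A reader might infer that the HHS is the only component scored at each hospital's own clinic, and so is open to differences between clinics. The article places HHS scoring at the outpatient clinic. It does not say that each hospital uses its own, nor where the other instruments are completed at follow-up, and it documents no scoring difference.
- The percentages for HHS-only effects might be read as error rates of the MANOVA. They are its power against a real HHS difference. The fault lies in reading such a rejection as evidence about ADL.

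**Conclusion.** The point holds as a mismatch between hypothesis and test. The trial is sized on one-sided 6-month Katz recovery, and the only inferential test named is non-directional and spans four outcomes. A significant joint p-value would show neither an ADL difference nor its direction. Over assumed correlations of 0 to 0.7, an HHS-only difference of 0.3 SD (0.4 SD) gives significance in 45–89% (73–99%) of trials, and Katz worse with HHS better by 0.2 SD each in 40–93%. The alternative reading, four tests each at 0.05, leaves about a 15–19% chance of at least one false positive at correlation 0.5 to 0. The effect sizes, the equal correlations and normality are my assumptions, since the documents give none. The probabilities depend on them; the conclusion that the joint test does not answer the ADL question does not.

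**What to change.** In the Statistical analyses section, state that effectiveness is judged on 6-month Katz recovery alone, adjusted for the propensity score and tested at the level given in the Sample size section. Report IADL, EQ-5D and HHS as secondary outcomes under a multiplicity rule stated in advance, for example Holm or a fixed order. State that the joint MANOVA p-value is not used as evidence of effectiveness on ADL.

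The cost is a change of wording. The sample size stays: the unadjusted comparison of 130 with 130 at one-sided 0.05 has 78.3% to 80.6% power for a 15-point difference over the assumed usual-care rates. The small downside is a stricter standard for secondary claims: under Holm they face a lower threshold, and under a fixed order that starts with Katz they cannot be claimed if Katz recovery is not significant.
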